### **2.7.2 Demographic and medical data.**

Data to be extracted from the Sciensano database are a list of all nursing homes in Belgium with their RIZIV number, postal code, the capacity of each nursing home (number of beds), and suspected (CT and symptoms) and confirmed (PCR and AG POC test) COVID-19 related death rate.

At the NH level, the management will be asked, at baseline, about the proportion of care grade (according to the Katz evaluation scale) among their residents, if a COVID-19 vaccination campaign was organized in the NH yet (date, type of vaccine and vaccination coverage), the suspected and confirmed COVID-19 infection rate, the COVID-19 related and non-COVID-19 related death rate from the beginning of the crisis until now and if and when they had an outbreak (more than one COVID-19 infection that are suspected to be related). With every follow-up sampling timepoint, the NH will be asked about a vaccination campaign (when this did not take place yet at baseline), if COVID-19 testing was performed in their NH, the respective proportion of positive tests and COVID-19 related death rate.

Individual medical data, comprising medical history and if participants have experienced an episode of COVID-19 symptoms or underwent a COVID-19 (PCR/antigen) test (with mention of date and result) or if COVID-19 was confirmed by a CT-scan, reason of missing data of drop outs (death, hospitalisation, sick leave, leaving the job), and whether they received a COVID-19 vaccination (date, type of vaccine, number of doses) in both NH residents and staff will be collected through an online questionnaire at both baseline and follow-up sampling timepoints (LimeSurvey) (See Appendix 6.3 for questionnaires). The CRC will fill out the questionnaire concerning the resident participants during the week of the sampling timepoint. Therefore the head of the nursing staff or the representative of the resident can be asked to provide the data. In this questionnaire, the surveyed medical data will be linked to the participant identification code. Concerning the medical history, the participants (NH staff and residents) will be asked

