### **Tertiary objectives**

Although this study was not designed to assess vaccine effectiveness, end points will be compared between vaccinated and non-vaccinated participants, applying propensity score methods, if sufficient non-vaccinated participants occur in the random selected sample.

8. To assess the risk of getting SARS-CoV-2 infected between vaccinated and non-vaccinated (at last visit) residents/staff.

If a sufficient number of non-vaccinated participants are available in the sample, a survival analysis will be performed to investigate the time (in days) to a SARS-CoV-2 infection

since 14 days after being fully vaccinated between vaccinated and non-vaccinated participants. A participant is considered to have an event when the participant had a reported positive PCR test result (or a positive antigen rapid test, or a positive CT scan, or a positive saliva test in absence of a PCR test) during the baseline or one of the follow-up visits. The survival or censoring time (in days) is registered since 14 days after being fully vaccinated (or since 14 days after main (second) vaccination date in corresponding NH in case of non-vaccinated participants) until first event (or censoring moment).

If the proportional hazard assumption holds, a stratified (by NH) Cox proportional hazards regression model will be used to model the hazard of SARS-CoV-2 infection between staff and residents, and between vaccinated and non-vaccinated participants, adjusting for history of self-reported SARS-COV-2 infections, and a time-varying NH vaccination degree. Propensity score methods will be applied to reduce the effects of confounding. If insufficient non-vaccinated residents would be available in the cohort, the analysis will be performed for staff only.

9. To assess the proportion of confirmed COVID-19 deaths and non-COVID-19 related deaths and the time until death (within the study timeframe) between vaccinated and non-vaccinated residents.

If sufficient non-vaccinated residents would be available, a survival analysis will be performed to investigate the time (in days) to a confirmed COVID-19 death since 14 days after vaccination (or since 14 days after main (second) vaccination date in corresponding NH in case of non-vaccinated participants). A non-COVID-19 related death will be considered as a competing risk in the analysis.

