## 6. Appendices

### 6.3 Appendix 3: Questionnaires (Dutch/French)

#### VRAGENLIJSTEN BIJ AANVANG VAN DE STUDIE

##### Vragenlijst woonzorgcentrum (in te vullen bij aanvang studie)

1. Studiereferentienummer van het woonzorgcentrum
2. Hoe is de verdeling in zorgcategorieën van de bewoners van het woonzorgcentrum (in absolute aantallen)?  
O:    A:    B:    C:    Cd:    D:
3. Vond er reeds een COVID-vaccinatieronde plaats in het WZC?
  - a. 1ste ronde / 2de ronde (datum)
  - b. Welk vaccin?
    - i. AstraZeneca/Oxford vaccin
    - ii. Het BioNtech-Pfizer vaccin
    - iii. Het Moderna vaccin
    - iv. Andere
2. Hoeveel bewoners werden gevaccineerd (in verhouding tot het totale aantal bewoners?)
3. Hoeveel medewerkers werden gevaccineerd (in verhouding tot het totale aantal medewerkers?)
4. Werd uw WZC getroffen door één of meerdere COVID-19 uitbraken (= meerdere besmettingen in dezelfde periode die – vermoedelijk - aan elkaar gelinkt kunnen worden) vanaf het begin van de crisis tot nu?
  - a. In welke periode /perioden werd het WZC getroffen?
  - b. Hoeveel personeelsleden en bewoners (bij benadering) werden toen in dezelfde periode positief getest?
5. Hoeveel vermoede of bevestigde COVID-19 besmettingen zijn er binnen het WZC geweest bij bewoners vanaf het begin van de crisis tot nu (bij benadering) (incl. overleden bewoners)?
6. Hoeveel vermoede of bevestigde COVID-19 besmettingen zijn er binnen het WZC geweest bij medewerkers vanaf het begin van de crisis tot nu (bij benadering)
7. Hoeveel bewoners zijn aan COVID-19 overleden vanaf begin crisis tot nu (bij benadering)?
  - a. Bevestigde COVID-19 overlijdens
  - b. Vermoedelijke COVID-19 overlijdens
8. Hoeveel bewoners zijn aan niet-COVID gerelateerde oorzaken overleden vanaf het begin van de crisis tot nu (bij benadering)

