## FOLLOW UP VRAGENLIJST

### Vragenlijst woonzorgcentrum

(in te vullen 2-maandelijks in de week dat de test afgenomen wordt)

1. Studiereferentienummer van het woonzorgcentrum.

*Vraag 2, 3 en 4 worden enkel toegevoegd indien bij de vorige vragenlijst neen werd geantwoord.*

2. Vond er reeds een COVID-vaccinatieronde plaats in het WZC?

2.3. 1ste ronde / 2de ronde (datum)

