## QUESTIONNAIRE DE SUIVI

### Questionnaire sur les foyers de soins résidentiels (à compléter tous les 2 mois dans la semaine où le test est administré)

1. Numéro de référence de l'étude du centre d'hébergement.

Les questions 2, 3, 4 ne sont ajoutées que si non dans le questionnaire précédent.

2. Une campagne de vaccination COVID a-t-elle déjà eu lieu au WZC?

3. . Date

a. 1er tour / 2ème tour (date)

b. Quel vaccin?

i. Le Vaccin AstraZeneca / Oxford

ii. Le vaccin BioNtech-Pfizer

iii. Le vaccin Moderna

iv. Autres

4. . Combien de résidents ont été vaccinés (par rapport au nombre total de résidents?)

. Combien d'employés ont été vaccinés (par rapport au nombre total d'employés?)

5.

6. Avez-vous eu des résidents / employés testés pour COVID-19 au cours des 2 derniers mois (entre le tour de test précédent et maintenant)?

7. Si c'est le cas,
  - Via le test PCR, combien?
  - Par le biais de tests antigéniques rapides, combien?
8. Si oui, qui vous a testé? Indiquez ce qui s'applique.
  - Résidents / employés présentant des symptômes
  - Un département / corridor (préventif, par exemple après contact avec le risque)
  - Tous les résidents / employés
  - Employés seulement
  - Résidents seulement
  - Autres combinaisons?: (Champ de texte ouvert)
9. Si oui, combien de résidents / employés ont été testés positifs?
 

Pour le test PCR:

Pour le test rapide:
10. Combien de résidents sont décédés du COVID-19 au cours des 2 derniers mois?
  - Nombre de décès COVID-19 confirmés
  - Nombre de décès suspects de COVID-19

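### Follow-up skip rule on the nursing-home form can leave the second-round date unrecorded, although it sets time zero for non-vaccinated participants in objectives 8 and 9

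*Protocol*

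**What the plan says.** **Time zero.** Under objective 8 (Protocol, 3.2, Tertiary objectives), survival time for vaccinated participants runs from 14 days after full vaccination. For the others it runs "since 14 days after main (second) vaccination date in corresponding NH in case of non-vaccinated participants". Objective 9 uses the same home-level anchor for non-vaccinated residents: "to investigate the time (in days) to a confirmed COVID-19 death since 14 days after vaccination (or since 14 days after main (second) vaccination date".

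**Where the date is requested.** The baseline nursing-home questionnaire (Appendix 6.3) asks "Vond er reeds een COVID-vaccinatieronde plaats in het WZC", that is, whether a vaccination round has already been held. Under it is the sub-item "1 ste ronde / 2 de ronde (datum", for the dates of the first and second rounds, followed by vaccine type and coverage.

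**When it is requested again.** The Dutch follow-up form says "Vraag 2, 3 en 4 worden enkel toegevoegd indien bij de vorige vragenlijst neen werd geantwoord". The French form says the same: "Les questions 2, 3, 4 ne sont ajoutées que si non dans le questionnaire précédent". Section 2.7.2 describes the rule as "With every follow-up sampling timepoint, the NH will be asked about a vaccination campaign (when this did not take place yet at baseline").

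**Model.** Both objectives use a Cox model stratified by nursing home. Both are to be run only if there are enough non-vaccinated participants.

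**The concern.** A non-vaccinated participant has no dose date, so the home's second-round date is the only time zero that the plan gives that person. The follow-up routing depends on whether *a* round has been held, while the analysis needs the date of the *second*. A home between its two rounds satisfies the routing question without yet being able to supply the date as a fact, and the block is then closed.

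In a model stratified by home, the vaccinated-versus-non-vaccinated comparison is made within each home. If a home's non-vaccinated participants cannot be placed on the time axis, that home adds nothing to this contrast. If they are placed by an assumed date, the error in that date decides which early events count as follow-up. The comparator group was never expected to be large: the table of changes reports that 15% of sampled staff were unvaccinated in the first test round.

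**Working it through.** The plan gives no figure to reproduce on this point. The check follows the skip logic and then asks whether the problematic state can occur.

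**1. Skip logic by the home's status**

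| Status at the visit | Answer | Second-round date |
|---|---|---|
| Both rounds held at baseline | yes | recorded at baseline |
| No round at baseline, both held by the first yes | no, then yes | recorded at that visit |
| First round only at baseline | yes | not yet a fact; block hidden at months 2 to 10 |
| No round at baseline, first round only at the first yes | no, then yes | not yet a fact; block hidden afterwards |

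Rows 3 and 4 are the gap. Row 3 follows from both forms and from section 2.7.2. Row 4 follows from the forms, which refer to the previous questionnaire. Section 2.7.2 refers to baseline and, read literally, would keep asking such a home.

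**2. Other sources in the protocol**

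- Individual forms, staff and residents, Dutch and French: the dose items ask for the date of the first injection only. At follow-up they appear only after an earlier no.
- A further follow-up item, to be used once applicable, asks for a vaccination date without a dose number.
- The Sciensano extract listed in 2.7.2 covers identifiers, postal code, capacity and COVID-19 deaths. It lists no vaccination dates.

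None of these records the home's second-round date.

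**3. Can a home be between rounds at baseline?**

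Inputs: campaign start 5 January 2021 (table of changes); baseline collection marked for February 2021 (Table 1), staggered over about four weeks (2.4). The interval between rounds is not in the documents, so it is assumed at 21, 28 or 84 days.

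Earliest second round = 5 January + interval: 26 January (21 days), 2 February (28 days), 30 March (84 days).

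A home is between rounds at visit date V if its first round was held by V but after V minus the interval:

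- V = 1 February: first round after 11 January (21 days) or after 4 January (28 days, so any home that had started).
- V = 28 February: first round after 7 February (21 days) or after 31 January (28 days).
- 84 days: every home that had started, throughout February.

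The state is therefore realistic across the whole baseline window.

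**4. Can the number of homes be fixed?**

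That needs the spread of first rounds as well as the interval, and the documents give neither. Assume, for illustration, visits V spread evenly over days 27 to 55 after 5 January:

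- First rounds even over days 0 to 21, interval 21 days: share = (15² / 2) / (21 × 28) = 112.5 / 588 = 0.19.
- First rounds even over days 0 to 42, interval 28 days: share = [E min(V, 42) − E max(V − 28, 0)] / 42 = (37.98 − 13.02) / 42 = 0.59.

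A range from 0.19 to 0.59 under equally arbitrary assumptions is not an estimate.

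**The case against.** **The comparator arm is not singled out.** A reader might infer that vaccinated participants in an affected home keep their time zero while only the comparators lose theirs. The documents do not support this. The individual forms explicitly request only the first-dose date, so a vaccinated participant's second-dose date is not explicitly recorded either, in any home. If it may be derived from the first dose plus an interval by vaccine type, the same derivation works for the home, whose form collects the round-1 date and vaccine type. This stands, and it removes any claim of a one-sided loss.

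**The date is neither unasked for nor unrecoverable.** The baseline form has a second-round field, so a scheduled date could be entered. Participants' reported dates might suggest a main date, and each home has a contact person and a visit every two months (2.7.3). This stands too. However, the protocol specifies none of these routes, and nothing prompts the home to confirm or correct a scheduled date.

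**The routing may be looser than it looks.** Section 2.7.2 speaks of a campaign, which could be read as incomplete until both rounds are done, and section 2.1 wants the home's vaccination degree updated at all timepoints. The forms, however, ask about a round, and their skip rule follows that answer. The stated intention to update makes the rule harder to defend.

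**A headcount is tempting.** Applying 15% to the planned 1380 staff gives 0.15 × 1380 = 207, of whom some share would be affected. This is not supported. The 15% is a first-round figure, whereas objective 8 classifies status at the last visit. The planned staff drop-out of 0.2 alone gives 0.8 × 207 ≈ 166 with complete follow-up, and later vaccination lowers it further.

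**Conclusion.** The conflict is real: the analysis requires a date that the follow-up form, used as written, stops requesting as soon as the first round has been reported. In any home that was between rounds at its first yes, the actual second-round date is not recorded by the planned forms. Comparators there either receive an approximated time zero (for instance, the round-1 date plus an assumed interval by vaccine type) or fall out of the home-stratified contrast. If the assumed interval were 21 days and the true one 28, their entry would be 28 − 21 = 7 days too early.

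The conclusion rests on reading the forms literally and on an interval between rounds long enough for some homes to be sampled between the two. Intervals of 21 days or more, which are an assumption, allow this. The number of homes and participants cannot be derived from the documents.

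The point is minor. It touches two tertiary analyses that depend on sufficient non-vaccinated participants, in a study that the protocol says was not designed to assess vaccine effectiveness. No primary or secondary analysis uses this comparator anchor. It is nonetheless wrong as written, because the protocol fixes both the time-zero definition and the routing, and a later analysis plan could only approximate a date that was not collected.

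**What to change.** Change the skip rule in section 2.7.2 and on the Dutch and French nursing-home follow-up forms. The second-round date should be asked at each follow-up until it has been recorded, whatever the previous answer about a round having been held. In homes already past the visit at which they first answered yes, ask once, retrospectively, for the second-round date.

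The cost is one routing change on two forms, the matching sentence in 2.7.2, and one question per affected home. No participant needs to be contacted and the analysis model does not change.

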## **4. Practical considerations**

### **4.1 Human resources and costs**

Personnel costs to manage and deliver the project both in Flanders and Wallonia to perform analysis of the collected data are budgeted for the total amount of 384 273,28 including a full time principal research associate at the university of Ghent and clinical research coordinators at each of the academic centers. The cost for the test material including the Orient Gene tests (10.6 euro per test) and test collecting material (alcohol swabs, lancets, others) is 229 897,80 euro. The costs related to statistical support is estimated at 45 302,40. Other costs (transportation, publication, fee for NH,... ) are estimated on 122 322,79. This brings the total up to 781 818,27 euro.

### **4.2 Quality assurance**

As for the questionnaire, this protocol will be reviewed by other researchers and experts in the field. The informed consent and the questionnaire will be available in two languages (French and Dutch). The sample collection and interpretation of the test result will be performed by trained researchers/CRC's. Data analysis will be done by the researchers of Ghent University.

### **4.3 Bias and limitations**

- Loss of follow-up or missing data is possible, for instance, when a NH staff-member is not present at the moment of sample collection or a sample was not collected due to heavy workload. In this case, effort will be made to contact the NH and collect the sample within two days after the sampling day. In case of, for instance hospitalization of NH resident or self-isolation of NH staff, missing test result data is inevitable. In order to prevent missing data in the online questionnaires, results will be monitored and effort will be made to remind participants to fill in the survey (by e-mail/telephonic contact or at the moment of testing).

- Underestimation of the presence of SARS-CoV-19 seroprevalence among this population due to:

- Testing method limitations, however, the COVID-19 IgG/IgM Rapid Test Cassette (Orient Gene Biotech Co.) provides good sensitivity (92,9%) and specificity (96,3%) (Sciensano, 2020).
- Data collection, however, researchers/CRC's in charge of collecting the samples will be trained to ensure correct use of the COVID-19 IgG/IgM Rapid Test Cassette and interpretation of the results to minimize reporting bias.

- Due to practical limitations, seroprevalence data cannot be collected at the same point in time in all participants in this study. Seroprevalence, however, is subjected to fluctuations of the infection rate in the current SARS-CoV-2 pandemic and is therefore also time-dependent. Therefore, the maximal difference between the first and last samples collected within the baseline collection round is set at  $\pm 4$  weeks days.

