## **2.5 Sample size**

To assess the cumulative incidence after 10 months of follow-up in residential care centers in Belgium a sample of 381 participants (residents & staff) is required to estimate a proportion of 0.5 with a half-width of 5%, using a 95% Wilson score CI. As residents/staff are clustered within care facilities, the sample size will be augmented by the design effect. Assuming, 15 participants (7 residents and 8 staff) per institution after 10 months of follow-up, and an ICC of 0.12, the design effect is  $2.68 = (1 + 0.12 \times (15 - 1))$ . The total sample size required is  $1022 = 381 \times 2.68$ . At least 69 institutions, each including 15 participants, need to be included in this study, which brings the total sample size to 1035 after 10 months follow-up. In order to obtain at least 15 participants, in 69 institutions after 10 months of follow-up, assuming a drop-out rate of 0.2 and 0.4 for staff (changes in staff, sick leave and holidays) and residents (deceased, hospitalized or transferred residents), would require 22 sero-negative participants per care facility, (10 staff, 12 residents) in all 69 institutions. Assuming a seroprevalence rate of 0.5 at the baseline moment of the study would require 44 participants per care facility, (20 staff, 24 residents) in all 69 institutions.

A final sample size calculation will be performed to check whether the sample size obtained for the second research question will be sufficient for the analysis of the first research question.

To assess the seroprevalence in residential care centers in Belgium a sample of 381 participants (residents & staff) is required to estimate a seroprevalence of 0.5 with a half-width of 5%, using a 95% Wilson score CI.

As residents/staff are clustered within care facilities, the sample size will be augmented by the design effect. Based on the previous calculation, 44 participants (24 residents and 20 staff) will be sampled per institution. Assuming an ICC of 0.12, the design effect is  $6.16 = (1 + 0.12 \times (44 - 1))$ . The total sample size required is  $2347 = 381 \times 6.16$ . At least 54 institutions, each including 44 participants, need to be included in this study, which brings the total sample size to 2376 participants.

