## **2.7 Data Collection**

### **2.7.1 Collection of capillary blood samples and point-of-care test procedures**

The capillary blood samples will be obtained using a lancet to finger prick the middle finger and collect a 1-10 drops of capillary blood. A capillary blood drop will be transferred to the

specimen well of a point-of-care (POC) test (COVID-19 IgG/IgM Rapid Test Cassette, Orient Gene Biotech Co.) using a plastic dropper (delivered with COVID-19 IgG/IgM Rapid Test kit). Two drops (ca. 80 µl) of Orient Gene Biotech sample buffer will be immediately added to the buffer well, with avoidance of air bubbles. If the red colour does not move across the test window or if blood is still present in the specimen well after two minutes, one additional drop of sample buffer should be added into the buffer well. The result should be read in 10 minutes, positive test results may be visible as soon as 2 minutes. The result cannot be interpreted after 15 minutes.

The results of the COVID-19 IgG/IgM Rapid Test Cassette should be interpreted as following:

- **Negative:** The coloured line in the control region (C) changes from blue to red. No line appears in the test line region M or G.
- **Anti-COVID-19 IgM positive:** The coloured line in the control region (C) changes from blue to red and a line appears in the test line M.
- **Anti-COVID-19 IgG positive:** The coloured line in the control region (C) changes from blue to red and a line appears in the test line G.
- **Anti-COVID-19 IgG and IgM positive:** The coloured line in the control region (C) changes from blue to red and a line appears in the test line G and M.
- **Invalid test:** Control line is still completely or partially blue and fails to completely change from blue to red. Insufficient specimen sample or incorrect procedural techniques are the most likely reasons for control line failure. The test should be repeated using a new cassette.

For the study any positive result of IgM or IgG will be considered as a positive result. In case of an invalid test, the test is repeated. When it is still invalid it will be noted as such. Additionally, a few drops of capillary blood will be collected on Dried Blood Spot (DBS) collection cards for (semi-)quantitative analysis of vaccine-induced/infection-induced anti-SARS-CoV-2- specific antibodies as a part of the sub-study performed by Ghent University (details are provided in appendix 6.4).

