#### **3.2 Statistical analysis**

##### **Primary objectives**

1. To assess the seroprevalence of SARS-CoV-2 among NH residents and staff in Belgium at month 0 and at every follow-up visit in the cohort at month 2, 4, 6, 8 and 10.

The seroprevalence of SARS-CoV-2 among NH residents and staff in Belgium at month 0, and follow-up in the cohort at month 2, month 4, month 6, month 8 and month 10, will be reported stratified for staff and residents, as well as a total seroprevalence with the 95% confidence interval (CI), assessed by a generalized equation estimation (GEE) analysis with independence covariance structure. The average seroprevalence in Belgian NH will be estimated via a generalized equation estimation (GEE) analysis with exchangeable covariance structure. All characteristics will also be displayed for the Belgian regions separately.

2. To assess the sero-incidence of SARS-CoV-2 among NH residents and staff in Belgium over five two month time frames and summarised over a ten month time period.

The sero-incidence of SARS-CoV-2 among NH residents and staff in Belgium over 5 two month time periods, as well as summarized over a period of 10 months, will be estimated as a total sero-incidence, as well as for NH residents staff separately, via a clustered Poisson (or binomial) regression, taking the clustered nature of participants within nursing homes into account.

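### Both primary outcomes use the rapid-test result with no correction for its stated error: this generally inflates sero-incidence, and biases seroprevalence by more than 5 points only above about 81%

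*Protocol*

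**What the plan says.** - Outcome (protocol 2.7.1): "For the study any positive result of IgM or IgG will be considered as a positive result". One cassette reading per visit therefore decides serostatus.
- Primary objective 1 (3.2): seroprevalence by group, "as well as a total seroprevalence with the 95% confidence interval (CI), assessed by a generalized equation estimation (GEE) analysis with independence covariance structure", plus an average over homes from a GEE with exchangeable structure.
- Primary objective 2 (3.2): sero-incidence over five two-month periods and over ten months, estimated "via a clustered Poisson (or binomial) regression, taking the clustered nature of participants within nursing homes into account". The section defines neither the risk set nor the seroconversion event.
- Test accuracy (4.3): the cassette "provides good sensitivity (92,9%) and specificity (96,3"%). This appears under the limitation "Underestimation of the presence of SARS-CoV-19 seroprevalence among this population due to". No limitation names false positives.
- Precision (2.5): cumulative incidence is sized "to estimate a proportion of 0.5 with a half-width of 5%, using a 95% Wilson score CI", and seroprevalence likewise "to estimate a seroprevalence of 0.5 with a half-width of 5%, using a 95% Wilson score CI". The calculation allows for clustering, drop-out and baseline positives, but not for test error.
- The only allowance for unreliable readings is a sensitivity analysis requiring two successive negative results. It applies to seroreversion (objectives 7 and 10 in 3.2), not to either primary objective.

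**The concern.** Neither primary estimator, as described, contains a term for test error, so each reading is treated as the participant's true status. The quoted specificity means that 3.7% of truly negative participants test positive at each visit, and the quoted sensitivity means that 7.1% of truly positive participants test negative.

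For a single cross-section these errors partly cancel. For sero-incidence they do not, because they add up in two ways. A true negative has five further chances of a false positive. A baseline false negative enters the at-risk group and is likely to be read as a seroconversion at the next visit. Results go to public health authorities after every testing round (4.4), so a sizeable sero-incidence could be reported when few or no participants have newly developed antibody.

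**Working it through.** **Inputs.** Se = 0.929 and Sp = 0.963 (4.3). Baseline seroprevalence 0.5, half-width 5 points, ICC 0.12, 69 homes of 44 participants, 15 per home left for incidence (2.5). Pilot values 24.5% for residents and 19.1% for staff (section 1). Five follow-up tests.

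**The plan's own figures reproduce.** The Wilson half-width at p = 0.5 first reaches 0.05 or less at n = 381. For the design effect, "and an ICC of 0.12, the design effect is" 1 + 0.12 × 14 = 2.68, so 381 × 2.68 gives 1022, or 69 homes of 15 (1035). For seroprevalence, 1 + 0.12 × 43 = 6.16, so 381 × 6.16 gives 2347, or 54 homes of 44 (2376). The sample-size arithmetic is not at fault.

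**Seroprevalence.** Apparent prevalence = 0.929p + 0.037(1 - p), so bias = 0.037 - 0.108p. It is zero at p = 0.037/0.108 = 34.3% and reaches -5 points at p = 0.087/0.108 = 80.6%.

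| True prevalence | Bias (points) |
|---|---|
| 0% | +3.7 (largest upward) |
| 19.1% | +1.6 |
| 24.5% | +1.1 |
| 50% | -1.7 |
| 80% | -4.9 |
| 85% | -5.5 |
| 90% | -6.0 |

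With all 3036 participants and design effect 6.16, the half-width at 50% is 1.96 × √(0.25 × 6.16/3036) = 4.4 points. Coverage of a nominal 95% interval is then about 92% at 24.5%, 88% at 50% and 15% at 85%.

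**Sero-incidence with nobody truly seroconverting.** Assume errors independent between visits and any first positive counted among baseline test-negatives.
- False negatives as a share of baseline test-negatives at p = 0.5: 0.5 × 0.071 / (0.5 × 0.071 + 0.5 × 0.963) = 0.0355/0.517 = 6.9%.
- First two months: 0.0687 × 0.929 + 0.9313 × 0.037 = 9.8%.
- Ten months: 0.0687 × (1 - 0.071^5) + 0.9313 × (1 - 0.963^5) = 0.0687 × 1.000 + 0.9313 × 0.172 = 22.9%.
- At 24.5% baseline the same formulas give 5.8% and 19.1%.

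**How the excess depends on the assumptions (ten months, 50% baseline).**
- True incidence, constant hazard: at 10%, 20% and 50% the observed values are 30.5%, 38.1% and 61.0%, an excess of 20.5, 18.1 and 11.0 points.
- Errors that persist within a person: take a beta-binomial with correlation 0.5 for both error types, conditional on the negative baseline reading, and no true seroconversion. The chance of at least one positive in five further tests is 1 - ∏(0.963 + i)/(1 + i) = 0.053 for a true negative and 1 - ∏(0.071 + i)/(1 + i) = 0.805 for a baseline false negative (i = 1 to 5). Apparent incidence is 0.0687 × 0.805 + 0.9313 × 0.053 = 10.4%. Over two months it is 4.9%.
- Only the month-10 test counted, independent errors: excess of +9.8, +6.4 and +1.4 points at true incidence 0, 20% and 50%.

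**The case against.** The strongest reply has four parts.

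*Seroprevalence.* A reader might infer that test error pushes both primary estimates beyond the planned ±5 points. The figures do not support that. At the planning value of 50% the bias is -1.7 points. It passes 5 points only above 80.6%, and there it is downward, as section 4.3 says. The pilot values in the upward range date from May 2020, whereas baseline sampling is scheduled for February 2021, after vaccination began, and only 15% of sampled staff were unvaccinated in the first round. This stands: in the likely range section 4.3 has the right direction for seroprevalence. It is incomplete rather than reversed, because it omits false positives.

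*Undefined event.* Section 3.2 does not say how a seroconversion is counted, and a statistical analysis plan, not shown here, could define it and add a correction. This stands as a limit on the size of the bias. Section 2.5 does size the incidence objective on participants seronegative at baseline, which fits the risk set used above, and the calculation counting only month 10 still shows an excess at low and moderate incidence.

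*Extreme case.* The 22.9% assumes no true seroconversion and independent errors. That is correct. It is a reference value rather than a forecast. Persistent errors roughly halve it.

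*Correction on weak inputs.* The protocol gives no validation sample size behind the accuracy figures and does not say whether they hold for vaccine-induced antibody. This stands, and it argues against replacing the crude estimate with an adjusted one.

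**Conclusion.** The point holds, chiefly for sero-incidence. Under the plan as written, the ten-month figure at 50% baseline seroprevalence is too high by 22.9 points when nobody seroconverts and by 11.0 points when half do, given independent errors and any-first-positive counting. With strongly persistent errors (correlation 0.5) the excess at zero true incidence is about 10 points. If only month 10 counts it runs from +9.8 points at zero incidence to +1.4 at 50%. Most of these exceed the planned 5-point half-width, but not all, and the last is small.

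For seroprevalence the bias is at most +3.7 points upward, small at 50%, and beyond 5 points only above 80.6% true prevalence. Vaccination makes that level plausible in this cohort, but the documents do not establish it. A general breach of ±5 for seroprevalence is therefore not shown. Section 4.3 needs correcting because it omits overestimation, which affects seroprevalence below about 34% and sero-incidence generally. Everything here rests on the two accuracy figures quoted in the protocol.

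**What to change.** 1. For both primary objectives, pre-specify a misclassification-adjusted estimate to be reported alongside the crude one. Give it over a stated range of sensitivity and specificity, including values for vaccine-induced antibody, and carry the nursing-home clustering into the interval.
2. For sero-incidence, define the risk set and the event. Add an analysis in which baseline seronegativity and each seroconversion count only when confirmed by the same-visit dried-blood-spot ELISA (appendix 6.4), or by a second successive rapid test where a later visit exists. Under independence, requiring two successive positives cuts false seroconversion among true negatives over five rounds from 17.2% to about 0.5% (four adjacent pairs × 0.037² = 0.55%, less a little overlap). It cannot confirm a conversion first seen at month 10, and using it for baseline status uses up the first interval, so the ELISA route is needed there. The ELISA's own accuracy should be stated.
3. Reword section 4.3: test error overestimates seroprevalence below about 34% true prevalence, underestimates it above, and generally overestimates sero-incidence.

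Cost: no new sampling, but wider intervals and dependence on assumed accuracy. With Se and Sp treated as known, the variance rises by 1/0.892² = 1.257, so 381 becomes 479. For seroprevalence 479 × 6.16 = 2951, or 68 homes, within the planned 69. The same scaling for incidence gives 479 × 2.68 = 1284, or 86 homes of 15, so with 69 homes the adjusted incidence interval would exceed ±5 points. That figure is only indicative, since repeated testing needs its own error model.
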